# 3. Study population

Young men and women aged 15-24 years living in the Africa Centre DSA

Eligibility criteria for enrollment:

- participants aged 15-24 years at the time of sampling
- resident at the time of the study
- willing to participate and able to provide informed consent

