# 4. Sample size

447 young men and women agreed to participate and provided informed consent. Details on sampling methods and intended sample size are provided in the excerpt of the study protocol (Version 1.3, 09 Sept 2016) below:

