# 8. Analyses

## 8.1 Primary Objective 1-Feasibility

Feasibility will be examined by sex and age group (15-19 and 20-24 years) using the following outcomes:

- proportion of selected individuals who were visited (regardless of the outcome of visit).
- proportion of visited individuals who were contacted after ≥1 contact attempt

The proportion of those who were not contacted and reasons for failing to contact individuals will also be summarized.

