## 8.3 Primary Objective 2-Prevalence of curable STIs, HSV2 and BV

The prevalence (and the 95% confidence interval) of *T. vaginalis*, HSV-2, syphilis, *N. gonorrhoeae*, *C. trachomatis* will be presented overall and separately for males and females and by age group.

Sampling weights will be applied to account for unequal probabilities of selection in the stratified sample design (335 individuals selected from each age group and sex stratum). Sampling weights will be calculated as the inverse probability of selection (i.e. number of individuals sampled in the stratum/ total individuals in the stratum); this will have the effect that participants in the under-represented strata get a larger weight and participants in the over-represented strata get less weights.

In addition, weights will be applied for non-response, calculated as the inverse probability of study participation in strata defined by age group, sex and residence location (urban/peri-urban/rural) using logistic regression. This will be done by combining the data from the entire sampled population with that from the study population, and performing a logistic regression with sex, age group & residence as predictors in the model, to get the predicted probability of participation. The inverse of this predicted probability will be used as the response weight, which will be combined with the sampling weight.

Variables:

- Any curable STIs (1-if diagnosed with at least one STI (chlamydia, gonorrhoeae, trichomoniasis, syphilis) 0-None)
- Chlamydia trachomatis (Presence/absence)
- Neisseria gonorrhoeae (Presence/absence)
- Trichomonas vaginalis (Presence/absence)
- Syphilis: negative (TP-/VDRL-); early or previously treated infection (TP+/VDRL-); active syphilis (TP+/VDRL+ low titer [<1:8]; TP+/VDRL+ high titer [≥1:8])
- HSV-2 (Presence/absence)
- Bacterial vaginosis (Presence/absence)

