## 8.4 Objective 3: Factors associated with the presence of curable STIs, HSV2 and BV among young men and women

### 8.4.1 Descriptive analysis - Baseline characteristics of participants

Variables will be summarized by sex and age group. Continuous variables will be summarized using means, standard deviations, medians and interquartile ranges; invalid or impossible values will be set to missing. Frequency counts and percentages will be used to summarize categorical variables.

Variables:

Demographic data

- Age at enrolment (years)
- Level of education completed (primary or less (grade 1-7), secondary (8-11), matric, graduate/postgraduate)
- Working or studying (Working, Studying, Not working or studying)
- Marital status (single, married, separated, living together (not married), civil union)

Alcohol, tobacco and drug use

- Ever smoked cigarette (Yes/No)
- Ever used smokeless products (Yes/No)
- Ever drunk alcohol (Yes/No)
- Drank at least one drink in the past month (Yes, No, Never drinks)
- Drank 5 or more drinks in the past month (Yes, No, Never drinks)
- Ever smoked cannabis (Yes/No)

Circumcision and genital hygiene (restricted to males)

- Circumcised (Yes/No)
- Age at circumcision (Infant, teenager, adult)
- Clean penis with bath soap (Yes/No)

Menstruation and hygiene (restricted to females)

- Menstruation started (Yes/No)
- Age at menarche (years). This will be summarized for individuals who have started menstruating
- Use sanitary pads during menstruation (Yes/No)
- Ever inserted substance in the vagina (Yes/No)
- Ever cleanse inside vagina (Yes/No)

Reproductive health (restricted to females)

- Ever been pregnant (Yes, No, never had sex)
- Age at first pregnancy (years)
- Contraceptive use (Yes/No)
- Contraception method (None, condoms, hormonal, other)

Sexual relationships

- Ever had sex (Yes/No)
- Age at first sex (years)
- In a sexual relationship (Yes/No)
- Used a condom at last sex (Yes/No)
- Drank alcohol before sex (Yes/No)
- Number of people you had sex with in the past 3 months
- Know your partner’s HIV status (Yes/No)

Medical history

- Have current RTI symptoms (Any symptoms, None)

Symptoms will be summarized separately for males and females.

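### The non-response model in SAP 8.3 uses age only as two five-year bands, so any non-response bias linked to age inside a band would not be corrected; a smooth term for age in years is a cheap improvement.

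*SAP*

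**What the plan says.** SAP section 8.3 combines two weights for the prevalence estimates.

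- **Sampling weight.** It corrects for unequal selection across age-by-sex strata, with "335 individuals selected from each age group and sex stratum".
- **Response weight.** It is the inverse of a predicted probability of participation, for "strata defined by age group, sex and residence location (urban/peri-urban/rural) using logistic regression". The plan obtains it by "performing a logistic regression with sex, age group & residence as predictors in the model". Non-participants also contribute, since the data set is built by "combining the data from the entire sampled population with that from the study population".

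Section 8.3 does not define age group. Section 8.1 does: "Feasibility will be examined by sex and age group (15-19 and 20-24 years". Prevalence is reported overall, by sex and by age group, so the weighting bands coincide with the sampling and reporting bands.

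Section 3 requires "participants aged 15-24 years at the time of sampling" and also residence at the time of the study. Section 7.1 gives migration as an example of a reason for non-contact. Section 4 reports that "447 young men and women agreed to participate and provided informed consent". Section 8.4.1 lists "Age at enrolment (years"), but as a descriptive variable for participants.

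**The concern.** Apart from any age difference between residence types, neither weight distinguishes a 15-year-old from a 19-year-old, or a 20-year-old from a 24-year-old. Weighting of this kind removes bias only if, within a weighting class, those who took part resemble those who did not.

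That condition could fail here. School-leaving and moving for work plausibly alter the chance of being found and taking part within these five-year spans. Sexual debut and exposure, and with them the prevalence of sexually acquired infections, plausibly change over the same years. The SAP itself treats age as an a priori confounder in every risk-factor model (section 8.4.2).

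About two thirds of those selected did not take part, so primary objective 2 leans on the response model. A residual bias would be systematic, and the 95% confidence interval would not show it.

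**Working it through.** The SAP states no bias figure and gives neither participation nor prevalence by single year of age. There is nothing to reproduce, and every gradient below is an assumption.

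**Participation.** Selected: 335 (section 8.3) x 4 strata = 1,340. Participants: 447 (section 4). 447/1,340 = 33.4%.

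**Formula.** Take five equally sized single-year ages a in a band, with participation r_a and prevalence p_a. Band-level weights give an expected estimate of sum(r_a p_a)/sum(r_a). The true value is mean(p_a). The difference is zero if either r or p is flat within the band.

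**Both bands together.** The two bands are averaged equally. Mean participation is 40% at 15-19 and 27.5% at 20-24, or 33.75% on average, close to the observed 33.4%.

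The steepest case takes prevalence rising linearly from 3% at age 15 to 45% at age 24, and participation falling from 55% to 25% in the younger band and from 35% to 20% in the older.

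- 15-19: sum(r p) = 0.2117 and sum(r) = 2.000, giving 10.6% against a true 12.3% (-14% relative).
- 20-24: sum(r p) = 0.4729 and sum(r) = 1.375, giving 34.4% against a true 35.7%.
- Overall: 22.5% against 24.0%, or -1.5 points.

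The simple standard error is sqrt(0.24 x 0.76/447) = 2.0 points. The shift is about 0.75 SE, and coverage of a nominal 95% interval is Phi(1.96 - 0.75) - Phi(-1.96 - 0.75) = 0.88.

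| Prevalence, age 15 to 24 | Participation within bands | Overall shift |
|---|---|---|
| 3% to 45% | 55% to 25%; 35% to 20% | -1.5 points |
| 3% to 45% | 45% to 35%; 30% to 25% | -0.5 points |
| 5% to 15% | 55% to 25%; 35% to 20% | -0.4 points |
| 5% to 15% | 45% to 35%; 30% to 25% | -0.1 points |
| any | flat within bands | 0 |

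**One band at a time, a second set of assumptions.** Mean participation is 33.4%, and the highest-to-lowest participation ratio across the band is 1.25 to 2, in either direction.

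| Prevalence across the band | Shift in that band |
|---|---|
| flat 10% | 0 |
| 8% to 12% | ±0.1 to 0.3 points |
| 4% to 16% | ±0.3 to 1.0 points |
| 2% to 30% | ±0.8 to 2.3 points |

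The sign follows the direction of the participation gradient. For comparison, 1.96 sqrt(p(1-p)/n) at p = 10% and 16% is 3.9 and 4.8 points for one band (n about 223), and 2.8 and 3.4 points overall (n = 447), ignoring any design effect. The shift is below the half-width in every scenario.

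**With age in years in a correctly specified model.** Take prevalence 4% to 16% and participation 44.5% falling to 22.2%. Band weights give 9.0%; single-year weights give the true 10.0%.

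**Cost in weight variability.** Use n sum(w²)/(sum w)², with ten equal age groups and equal sampling weights. With w = 1/r this reduces to sum(r) x sum(1/r)/10².

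- Band weights: 3.375 x (5/0.40 + 5/0.275)/100 = 1.04.
- Single-year weights, steep participation gradient: 3.375 x 32.40/100 = 1.09.
- Single-year weights, mild participation gradient: 1.04.

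**The case against.** Four arguments count against pressing this hard.

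**Weighting cells aligned with the sampling and reporting strata are common and defensible.** Any response model could be given finer covariates. This stands: the SAP contains no contradiction or mistake here. But the plan already fits a regression, so a smooth age term needs no extra cells.

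**The bias is conditional.** It requires both participation and prevalence to vary with age inside a band, and the SAP shows neither. The largest figure needs a fifteen-fold rise in prevalence together with participation more than halving at 15-19. This stands too. Staying inside the interval half-width is not full reassurance, since a shift of 0.75 SE already lowers coverage to about 88%, but nothing in the SAP singles out that scenario.

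**Some non-participants may not belong to the target population.** Section 3 requires residence at the time of the study, and section 7.1 mentions migration. If the fall from 55% to 25% at 15-19 were entirely out-migration, with flat response among residents, 10.6% would be the correct resident prevalence, and single-year weights over everyone sampled would wrongly move it to 12.3%. The 33.4% is thus a yield on all selected, not a shown response rate among eligible residents. This limits what can be said about direction and size. It applies equally to the band-level model, so it argues for care over who enters the model, not for keeping the bands.

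**Age for every sampled person is not stated to be available.** Correct: section 8.4.1 lists age in years for participants only. Still, eligibility at sampling and stratum membership must both be determined from age or birth date on the frame, so availability is a strong inference.

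**Conclusion.** The point holds as a low-cost improvement. The response model in section 8.3 cannot correct differential participation by age within 15-19 or within 20-24. If prevalence also varies with age there, the corresponding bias would remain. Under the assumed gradients it runs from zero to about 1.5 points overall, and 0.1 to 0.5 points in all but the steepest case.

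A reader might infer more than this:

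- **That the estimates are biased.** The SAP gives no single-year participation or prevalence, so this is not established.
- **That they are too low.** The negative signs in the overall scenarios come from assuming that participation falls with age; if it rises, they reverse. Out-migration clouds the direction further.
- **That every infection is affected.** This would need a within-band age gradient for each one, which the SAP does not show.

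The sizes assume equally sized single-year ages, linear gradients, equally weighted bands and simple standard errors. The claim that the remedy removes the bias assumes a correctly specified age term and a model fitted to eligible people.

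**What to change.** In section 8.3:

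1. Replace age group in the response model with age in years at sampling, as a linear term or a spline, alongside sex and residence. Take it from the surveillance frame used to determine eligibility and strata, and confirm that it is held for all 1,340. A smooth term is preferable to single-year cells: 447 participants over 10 ages x 2 sexes is about 22 per cell.
2. State who enters the model: sampled people not known to be ineligible, for example not known to have moved out of the area.
3. Keep 15-19 and 20-24 for the sampling strata and for reporting.

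The cost is one changed term and one sentence on the analysis set. Weights become slightly more variable: the weighting design effect rises from about 1.04 to at most about 1.09 in the assumed scenarios. If participation is flat in age, the results will hardly change.

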## 8.4 Objective 3: Factors associated with the presence of curable STIs, HSV2 and BV among young men and women

### 8.4.1 Descriptive analysis - Baseline characteristics of participants

Variables will be summarized by sex and age group. Continuous variables will be summarized using means, standard deviations, medians and interquartile ranges; invalid or impossible values will be set to missing. Frequency counts and percentages will be used to summarize categorical variables.

Variables:

Demographic data

- Age at enrolment (years)
- Level of education completed (primary or less (grade 1-7), secondary (8-11), matric, graduate/postgraduate)
- Working or studying (Working, Studying, Not working or studying)
- Marital status (single, married, separated, living together (not married), civil union)

Alcohol, tobacco and drug use

- Ever smoked cigarette (Yes/No)
- Ever used smokeless products (Yes/No)
- Ever drunk alcohol (Yes/No)
- Drank at least one drink in the past month (Yes, No, Never drinks)
- Drank 5 or more drinks in the past month (Yes, No, Never drinks)
- Ever smoked cannabis (Yes/No)

Circumcision and genital hygiene (restricted to males)

- Circumcised (Yes/No)
- Age at circumcision (Infant, teenager, adult)
- Clean penis with bath soap (Yes/No)

Menstruation and hygiene (restricted to females)

- Menstruation started (Yes/No)
- Age at menarche (years). This will be summarized for individuals who have started menstruating
- Use sanitary pads during menstruation (Yes/No)
- Ever inserted substance in the vagina (Yes/No)
- Ever cleanse inside vagina (Yes/No)

Reproductive health (restricted to females)

- Ever been pregnant (Yes, No, never had sex)
- Age at first pregnancy (years)
- Contraceptive use (Yes/No)
- Contraception method (None, condoms, hormonal, other)

Sexual relationships

- Ever had sex (Yes/No)
- Age at first sex (years)
- In a sexual relationship (Yes/No)
- Used a condom at last sex (Yes/No)
- Drank alcohol before sex (Yes/No)
- Number of people you had sex with in the past 3 months
- Know your partner’s HIV status (Yes/No)

Medical history

- Have current RTI symptoms (Any symptoms, None)

Symptoms will be summarized separately for males and females.

### 8.4.2 Multivariable analysis

Logistic regression models will be used to examine the association between exposure variables and the outcomes. The magnitude of association between exposure and outcome will be summarized using odd ratios and 95% confidence intervals. The model will be built using a conceptual hierarchical framework with three levels: sociodemographic, behavioral and sexual behavior ([1](#_ENREF_1)). Age and sex will be considered a priori confounders and included in all models. First, sociodemographic variables whose age and sex-adjusted association with the outcome is significant at p<0.10 will be added to the model (one at a time). Those that remain significant at p<0.10 will be retained. Behavioral factors will then be added to this model one at a time, and retained if they remain associated at p<0.10. Sexual behavior variables will be handled in the same way. Both crude and adjusted odd ratios will be presented. Many of the sexual behavior variables are only asked of individuals who are sexually active; therefore, the analysis of these variables will be restricted to that sub-group.

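### Residence location is held for every sampled person but is neither listed nor fixed as an adjustment variable in the risk-factor models, which may modestly confound the odds ratios

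*SAP*

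**What the plan says.** SAP section 8.4.2 sets out the risk-factor analysis: "Logistic regression models will be used to examine the association between exposure variables and the outcomes". On fixed adjustment it says: "Age and sex will be considered a priori confounders and included in all models". Other variables enter through a "conceptual hierarchical framework with three levels: sociodemographic, behavioral and sexual behavior". At the first level, a variable must pass a p<0.10 screen adjusted for age and sex, and must then stay below p<0.10 to be kept. The section does not list the members of the sociodemographic level, and it does not mention weights.

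Section 8.4.1 lists the variables to be described under Objective 3. Its demographic items are age, completed education, working or studying, and marital status. Residence is not among them.

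Residence appears only in section 8.3, in the non-response weights for prevalence. The method there is "performing a logistic regression with sex, age group & residence as predictors in the model, to get the predicted probability of participation", fitted to data on everyone sampled. So residence is known for every selected person, and therefore for all 447 participants.

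**The concern.** Objective 3 is to investigate risk factors for reproductive tract infections. Whether a young person lives in an urban, peri-urban or rural area plausibly affects schooling, employment and alcohol use, and separately the chance of infection. If both links exist, an odds ratio for schooling, work or alcohol that is adjusted only for age and sex carries part of the residence effect. Residence is also a standard sociodemographic risk factor in its own right. As the plan stands, nothing requires its association with infection to be estimated or reported.

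The variable is already in hand, so the omission is cheap to correct before analysis. Correcting it after the results are known would look like a choice driven by the data.

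**Working it through.** The SAP gives no power calculation or target odds ratio (OR) for Objective 3, so there is no planned figure to reproduce. The check compares the sections and then illustrates the possible bias.

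**1. The sections side by side.** Variables fixed in the regressions (8.4.2): age, sex. Demographic variables listed (8.4.1): age, education, working or studying, marital status. Predictors of participation (8.3): sex, age group, residence. Residence is in the third set only.

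**2. Participation.** Section 8.3 gives 335 selected in each age-by-sex stratum, so 4 × 335 = 1,340. Section 4 gives 447 participants. 447/1,340 = 33.4%.

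**3. Illustration of confounding.** All inputs in this step are assumed:
- Residence shares (urban/peri-urban/rural): 10/30/60% or 33/33/34%.
- Rural reference: exposure 30%, infection 12% in the unexposed.
- Urban-against-rural OR, R, the same for exposure and for infection: 1.5, 2 or 3. Peri-urban takes √R.
- Participation by residence: equal, 20/30/40% or 40/35/25%.
- True exposure–infection OR within each residence level: 1.0 or 2.0.

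For each level, odds = reference odds × R (urban), √R (peri-urban) or 1 (rural), and probability = odds/(1 + odds). The 2×2 tables are summed over residence, and OR = (a × d)/(b × c).

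Worked case: R = 3, shares 33/33/34%, true OR 1.0, equal participation.
- Exposure: 56.25%, 42.60%, 30.00%. Infection: 29.03%, 19.11%, 12.00%.
- Exposed and infected: 0.33 × 0.5625 × 0.2903 + 0.33 × 0.4260 × 0.1911 + 0.34 × 0.30 × 0.12 = 0.0930.
- By the same sums: exposed and uninfected 0.3352, unexposed and infected 0.1067, unexposed and uninfected 0.4651.
- OR without residence = (0.0930 × 0.4651)/(0.3352 × 0.1067) = 1.21. Within each residence level it is 1.00.

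ORs with residence left out:

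| Residence OR with exposure and infection | True OR 1.0, full sample | True OR 1.0, participants | True OR 2.0, participants |
|---|---|---|---|
| Unrelated to exposure, to infection, or to both | 1.00 | 1.00 | 1.98–2.00 |
| 1.5 | 1.02–1.03 | 1.02–1.03 | 2.03–2.05 |
| 2 | 1.06–1.08 | 1.05–1.08 | 2.08–2.14 |
| 3 | 1.16–1.21 | 1.13–1.21 | 2.22–2.36 |

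With residence in the model, the OR equals the true value in every case.

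**4. Confounding or selection?** The shift is already present in the full sample, where everyone takes part. Differential participation by residence changes it by about 0.03 at most for a true OR of 1.0 (1.162 to 1.130) and about 0.06 at most for 2.0 (2.276 to 2.220).

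**5. Sensitivity to the set-up.** Take two residence levels with 30% non-rural, infection 30% against 15%, exposure 50% against 25% and no true effect. The cells are 0.07125, 0.25375, 0.12375 and 0.55125, and the OR is (0.07125 × 0.55125)/(0.25375 × 0.12375) = 1.25. With 447 people the cell counts are 31.8, 113.4, 55.3 and 246.4. The standard error of the log OR is √(1/31.8 + 1/113.4 + 1/55.3 + 1/246.4) = 0.250, and the 95% interval extends by a factor of exp(1.96 × 0.250) = 1.63 either side.

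**6. Would the p<0.10 screen bring residence in?** Assume infection 25% non-rural against 15% rural, with 30% non-rural, so 18% overall.
- n = 447 (134 and 313): null SE √(0.18 × 0.82 × (1/134 + 1/313)) = 0.0397; alternative SE √(0.25 × 0.75/134 + 0.15 × 0.85/313) = 0.0425. Chance of passing ≈ Φ((0.10 − 1.645 × 0.0397)/0.0425) = Φ(0.82) ≈ 79%.
- n = 220, an assumed single-sex subgroup (66 and 154): the SEs are 0.0565 and 0.0606, giving Φ(0.12) ≈ 55%.

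**The case against.** The strongest reply is that the SAP does not shut residence out. Section 8.4.1 is headed as a descriptive analysis and does not claim to be the candidate list. Sex is not an item on that list either, yet section 8.4.2 fixes it in every model. The sociodemographic level is left open, so residence could be taken as a member. This stands: a reader might infer that residence cannot enter even as a candidate, and the text does not say that. The defect is that residence is unnamed and not fixed. Entry by p-value would be weak protection against confounding, especially in single-sex models.

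A reader might also infer selection bias, because the plan itself models participation on residence and only a third of those sampled took part. The documents do not support this. Predicting participation does not make a variable a confounder; it must relate to both exposure and infection. If it is unrelated to either, a true OR of 1.0 stays at 1.0 under every participation pattern tried. It is likewise not a general rule that an unweighted regression is sound only if it conditions on all three participation variables. Participation that depends on sexual behaviour or infection would not be corrected by adding residence.

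Using different variables for prevalence and for association is not in itself inconsistent, since the two analyses answer different questions. Silence on weights in 8.4.2 is also not a statement that none will be used.

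Finally, the bias is assumed rather than measured, and education, work and marital status may absorb part of it if they are retained. In the milder scenarios it lies well within sampling error for 447 people. All of this limits the size of the point. It gives no reason to leave out a variable that is already held.

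**Conclusion.** The point holds as one of confounding control and completeness. The plan fixes only age and sex, does not name residence in its Objective 3 variables, and already has residence for everyone. The plausible effect is modest: a null OR would read about 1.02 to 1.08 if residence ORs with exposure and infection are 1.5 to 2, and up to about 1.2 if they are 3. The two-level case with larger assumed contrasts gives 1.25. Every figure rests on assumed residence shares, exposure and infection frequencies, because the SAP reports none. If residence is unrelated to the exposure or to infection, there is no confounding to remove; the 1.98 for a true OR of 2.0 in that row reflects non-collapsibility of the OR. The main gain is a pre-stated adjustment and a reported estimate for a standard risk factor.

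**What to change.** - Section 8.4.1: add residence location (urban, peri-urban, rural) to the demographic variables.
- Section 8.4.2: make residence location an a priori covariate alongside age and sex, present in every model without passing the p<0.10 screen, and report its own crude and adjusted odds ratios.
- For rare outcomes or single-sex models, allow urban and peri-urban to be combined, and state this in advance.
- Optional: state whether the section 8.3 weights apply to the regressions. If they do not, show the final models with the weights as a sensitivity analysis.

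The cost is about two degrees of freedom per model, or one where categories are combined, with some loss of precision for rare outcomes. No new data are needed.
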